## Abstract

**Background:**

Common mental disorders are the most prevalent of all mental disorders, with the highest burden in terms of work absenteeism and utilization of health care services. Evidence-based treatments are available, but recognition and treatment could be improved, especially in the occupational health setting. The situation in this setting has recently changed in the Netherlands because of new legislation, which has resulted in reduced sickness absence. Severe mental disorder has now become one of the main causes of work absenteeism. Occupational physicians (OPs) are expected to take an active role in diagnosis and treatment, and seem to be in need of support for a new approach to handle cases of more complex mental disorders. Psychiatric consultation can be a collaborative care model to achieve this.

**Methods/design:**

This is a two-armed cluster-randomized clinical trial, with randomization among OPs. Forty OPs in two big companies providing medical care for multiple companies will be randomized to either the intervention group, i.e. psychiatric consultation embedded in a training programme, or the control group, i.e. only training aimed at recognition and providing Care As Usual. 60 patients will be included who have been absent from work for 6–52 weeks and who, after screening and a MINI interview, are diagnosed with depressive disorder, anxiety disorder or somatoform disorder based on DSM-IV criteria. Baseline measurements and follow up measurements (at 3 months and 6 months) will be assessed with questionnaires and an interview. The primary outcome measure is level of general functioning according to the SF-20. Secondary measures are severity of the mental disorder according to the PHQ and the SCL-90, quality of life (EQ-D5), measures of Return To Work and cost-effectiveness of the treatment assessed with the TiC-P. Process measures will be adherence to the treatment plan and assessment of the treatment provided by the Psychiatric Consultant (PC) in both groups.

**Discussion:**

In the current study, a psychiatric consultation model that has already proved to be effective in the primary care setting, and aimed to enhance evidence-based care for patients with work absenteeism and common mental disorder will be evaluated for its efficacy and cost-effectiveness in the occupational health setting.

## Background

Common mental disorders, i.e. depressive disorder, anxiety disorder and somatoform disorder, are the most prevalent of all mental disorders, with the highest burden in terms of work absenteeism and utilization of health care services [1-3]. In the case of depressive disorder, 80% of the costs are due to production loss [4]. People with major depressive disorder are absent from work 8 to 9 times as often as people without this disorder[5,6]. Mental problems account for 30% of disability leave, and in the majority of cases the employees have never been diagnosed or treated by a psychiatrist[7]. Complaints of the musculoskeletal system account for another 40%, and are considered to be possibly unrecognized somatoform, depressive and anxiety disorder[8]. Anxiety disorders such as generalized anxiety disorder and panic disorder, are also highly prevalent, and have a high societal impact[9]. Moreover, on average, absence from work due to mental disorders has a longer duration than absence caused by physical illness[10,11].

Guidelines for evidence-based treatments are available for depressive disorder, anxiety disorder and somatoform disorder[12-15,30]. However, for patients with these disorders in the primary care setting there is an inadequate offer of diagnostic and therapeutic help[16]. They often do not receive treatment, and present in the primary care setting with medically unexplained symptoms, thus burdening the General Practitioner (GP) and the health care setting in general with numerous visits and referrals to medical specialists[17-20]. The GP is misdirected by the combination of the patient's presentation with these symptoms and the fact that he has to meet competing demands in his practice[21]. If a mental disorder is recognized, the feasibility of these guidelines appears to be low, because many GPs feel incapable of delivering the cognitive behavioural interventions described in the guidelines, and also because of frequent care avoidance by the patients[22,23]. Therefore, care as usual (CAU) often implies fragmented patient-led care that is not cost-efficient, including referral to medical specialists to exclude somatic disease. This is a pity, because most of these patients can be treated effectively[24-27] in the primary care setting, if recognition and treatment is enhanced.

In the occupational health setting, that can be considered to have similar characteristics in terms of prevalence, diagnosis and treatment of mental disorders, as the primary care setting, a similar situation exists, but less attention has been paid to the diagnosis and treatment of common mental disorders. Guidelines for mental disorders in occupational health have been developed by the Dutch Association for Occupational Health (NVAB): guidelines for mental complaints[28], and, supplementary to the multidisciplinary guidelines for the diagnosis and treatment of depression[29], a module for depression and work. Guidelines have also been developed for the treatment of somatoform disorder in the occupational setting[30]. The NVAB guidelines for mental complaints[28] focus on stress and adjustment disorders in relation to the process of returning to work, functioning and the treatment of work-related problems. However, adequate recognition, treatment and criteria for the referral of patients for specialist treatment of mental disorders are not an important part of the guideline.

The implementation of the NVAB guidelines so far has led to a reduction in minor mental problems and in short-term work absenteeism. However, the amount of mental problems leading to disability leave remains high, indicating that occupational physicians (OPs) are still not accustomed to the diagnosis and treatment of mental disorders. In the Dutch legislation, responsibility for medical treatment is separated from responsibility for guidance in sickness absence and return to work (RTW). Only recently the OPs in the Netherlands have been enabled by law to refer employees to curative medical specialists if such treatment for a present mental disorder is needed for good functioning or RTW. Very little research has yet focussed on interventions for patients with common mental disorders, specifically aimed at RTW[3,31]. For many years it was assumed that recovery from symptoms would automatically lead to a recovery of functioning at work. However, it appears that focussing on functioning in the work setting contributes to a faster and a more lasting RTW in patients with mental disorders[32]. Thus, treatment of common mental disorder should not only focus on symptoms, but also on work-related functioning. This implies a broadening of the focus from the individual patient to the patient and the work context. Recovery should therefore also include the work setting: patients resume their work as soon as possible and are supported in this by their therapist [24]. For example, in a study carried out by Van der Klink et al. [25] among patients with adjustment disorders, in which the intervention was provided by OPs, the intervention had a shorter duration of sick leave than the control group. Therefore, in the present study we try to deal with sickness absence by embedding the treatment in the occupational setting and by including an intervention provided by the OP, after a consultation with a psychiatrist. Stimulating patients in RTW requires an active approach that encompasses specific interventions tailored to the needs created by the specific common mental disorder that the patient suffers from.

To summarize, in the present study design the following elements are central: training of OPs in the diagnosis and treatment of employees with depressive disorder, anxiety disorder or somatoform disorder; supportive psychiatric consultation aimed at the formulation of a diagnosis and a treatment plan, including suggestions for RTW adapted to the specific needs of the patients due to their specific disorder; and training of the consultant psychiatrists to provide not only a diagnosis and a treatment plan, but also to provide suggestions for successful strategies aimed at the improvement of work functioning.

## Methods/Design

### Objectives

The primary aim of the present study is to test the effectiveness of psychiatric consultation embedded in a training program for OPs, aimed at the diagnosis and treatment of common mental disorders in employees who are on sick leave, with a focus on work functioning. The secondary aim is to estimate the cost-effectiveness of the intervention.

### Hypothesis

In a randomized controlled study comparing psychiatric consultation with CAU provided by the OP, patients in the intervention group will improve in terms of general functioning, RTW, severity of the mental disorder and quality of life.

### Study design

The study is a two-armed cluster-randomized pragmatic clinical trial with randomization among the OPs. This intervention cannot be blinded, so the OPs might also use the techniques that they learned in the intervention to treat control patients. Randomization among OPs eliminates the danger of such contamination, and thus dilution of the effect. The outcome parameters will be measured by a blinded research assistant. This procedure has already been reported in detail elsewhere[33].

### Recruitment of OPs and consultant psychiatrists

The study has been designed and will be carried out in co-operation with ArboNed, and Arbounie, two companies providing company medical care. Together they cover almost half of the working population in the Netherlands. Within these two companies, 40 OPs from four offices in two regions will be recruited. Four consultant psychiatrists will also be recruited.

### Recruitment of patients

The aim is to include employees who have been absent from work for a minimum of 6 weeks and a maximum of 52 weeks, do not plan to resume work within the coming 6 weeks, and have been screened on either the Patient Health Questionnaire (PHQ) or the Whitely Index.

All patients who visited an OP within the past 6 months will be selected from the medical files, and will receive a letter describing the purpose of the study, together with an informed consent form for the screening procedure and the baseline questionnaires. Patients visiting an OP during the inclusion period will also be invited to participate in the study. They will also receive the informed consent form, together with the baseline questionnaires.

Patients will be included if they reach a cut off score of >15 on the PHQ9[34] or > 3.5 on the Whitely Index[35] and have given informed consent for participation in the study. The Mini-International Neuropsychiatric Interview (MINI.)[36,37] will be administered for the classification of symptoms according to DSM-IV[38]. In the intervention group, the patients selected in this way will have a consultation with a psychiatrist in addition to the treatment provided by the OP; in the control group the patients receive CAU provided by their OP.

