### Exclusion criteria

Patients will be excluded from the study if they are suicidal, psychotic or suffering from dementia, have insufficient knowledge of the Dutch language to fill in the questionnaires, or are addicted to drugs or alcohol. Patients who are already receiving psychiatric treatment can be included if mutual agreement is achieved with their current care-giver. Patients will also be excluded if they are involved in legislative procedures for unemployment compensation. (See Figure 1 for a flowchart of the participants.)

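### Inviting patients as they visit a randomised, unblinded OP leaves room for recruitment bias that the file-based letter route would largely avoid

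*Protocol article*

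**What the plan says.** **Allocation and blinding.** The Study design section states: "The study is a two-armed cluster-randomized pragmatic clinical trial with randomization among the OPs". On blinding it says: "This intervention cannot be blinded, so the OPs might also use the techniques that they learned in the intervention to treat control patients". Randomising OPs is presented as the remedy for that contamination. The only blinding described is at outcome: "The outcome parameters will be measured by a blinded research assistant". Under Treatment in the control group, half of the OPs are controls and their patients get care as usual, so a patient's arm is the OP's arm.

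**Routes of entry.** The Recruitment of patients section gives two. The first is retrospective and covers everyone: "All patients who visited an OP within the past 6 months will be selected from the medical files", followed by a letter with a consent form. The second is prospective: "Patients visiting an OP during the inclusion period will also be invited to participate in the study". These patients also receive the consent form and baseline questionnaires. The article does not say who invites them.

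**Entry criteria.** Some are scored: PHQ-9 above 15 or Whitely Index above 3.5, with a MINI interview for DSM-IV classification. One is the employee's own intention: "do not plan to resume work within the coming 6 weeks". Others, under Exclusion criteria, have no stated score or assessor, among them suicidality and addiction. Patients already in psychiatric treatment "can be included if mutual agreement is achieved with their current care-giver".

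**Timing and analysis.** Time-frame of the study places OP recruitment before a joint 12-month inclusion and intervention phase and gives no date for randomising the OPs. The Analysis section plans a multilevel analysis, with propensity scores and listed confounders to handle imbalance.

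**The concern.** Randomising OPs balances OPs. It balances patients only if the way patients come in does not depend on the OP's arm. In a cluster trial with open allocation that condition must be protected separately, and the one safeguard described, blinded outcome measurement, acts after entry.

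The letter route is close to neutral: the list is drawn from past visits and everyone on it is written to. The visit route is different. It runs throughout a phase in which intervention is already under way, and contact takes place around a consultation with an OP who may know the arm. Three things could then differ between arms: who is invited, who consents (a patient who knows that a psychiatric consultation is on offer may decide differently from one who knows it is not), and how the unscored exclusions and the care-giver agreement are settled.

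At stake is the primary comparison on the SF-20, and also return to work. A difference in prognosis at entry would appear as a treatment effect or would mask one. With 60 patients in all, a few differently chosen patients matter: three are 10% of an arm of 30.

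**Working it through.** The article gives no figure for this risk, so there is none to reproduce. The check has two parts.

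**1. Do the stated steps leave an opening?**

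| Step | What the article fixes | Protected against knowledge of arm? |
|---|---|---|
| Letter to patients of the past 6 months | All are selected from files | Largely, for invitation |
| Invitation at visits during inclusion | Patients are invited; inviter not named | Not stated |
| PHQ-9 / Whitely cut-off | Patient-completed, same threshold in both arms | Largely |
| MINI | Structured interview | Partly |
| Suicidality, addiction, care-giver agreement | No score or assessor named | Not stated |
| Consent | Required | Not stated |
| Outcome measurement | Blinded research assistant | Yes |

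The opening exists only if allocation is known when patients enter. The joint inclusion and intervention phase points that way: if patients are being treated by arm while others are still entering, at least some OPs are already allocated. The training does not help to settle it, because the Training section gives it to all OPs.

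**2. How much could it matter?**

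Inputs:
- 30 patients per arm (Sample size section).
- Intraclass correlation 1.0 and 3 patients per OP (Sample size section), giving a design effect of 1 + (3 − 1) × 1.0 = 3.
- 40 OPs and 60 patients (Recruitment of OPs; Abstract), so 60/40 = 1.5 patients per OP.
- Assumed: an arm difference in baseline prognosis of 0.2 to 0.5 SD among affected patients, and a correlation of 0.4 to 0.6 between that prognosis and the 6-month SF-20. The documents give neither.
- Assumed: either all patients are affected, or only half, since letter-route patients should be affected little.
- Assumed: two-sided test at 5%.

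Bias on the outcome, b = baseline shift × correlation:
- All affected: 0.2 × 0.4 = 0.08 SD up to 0.5 × 0.6 = 0.30 SD.
- Half affected: 0.04 to 0.15 SD.

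Standard error of the difference, in SD units, SE = √(2/30 × design effect):
- No clustering: √(2/30) = 0.258.
- Protocol's own planning values: √(2/30 × 3) = 0.447.

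False-positive rate with no treatment effect = 1 − Φ(1.96 − b/SE) + Φ(−1.96 − b/SE):

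| b (SD) | Unadjusted, unclustered | Intraclass correlation 1.0, 3 per OP |
|---|---|---|
| 0.04 | 5.3% | 5.1% |
| 0.08 | 6.1% | 5.4% |
| 0.15 | 8.9% | 6.3% |
| 0.30 | 21.3% | 10.3% |

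With an assumed intraclass correlation of 0.05 and 1.5 patients per OP, the design effect is 1 + 0.5 × 0.05 = 1.025, SE is 0.261, and the rate at 0.30 SD is 20.9%. Mild clustering therefore hardly changes the unclustered figures. The larger standard error in the last column lowers the false-positive rate but leaves the bias in the estimate as it is.

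**The case against.** The strongest case on the other side has four parts.

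**The text gives OPs no gatekeeping role.** A reader might infer that intervention OPs will put forward patients they expect to benefit. The article does not support this: it says that visiting patients will be invited, not by whom, and it does not say that OPs apply the exclusions. Nor is the six-week criterion an OP judgement; it is the employee's plan. It is equally tempting to read the care-giver agreement as concerning the extra consultation that only intervention patients receive. The Exclusion criteria section does not say what is agreed and does not limit it to one arm. These objections stand.

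**Scored filters are in place.** The same patient-completed cut-offs and a MINI apply in both arms. This stands as a limit on the risk. It does not govern who is approached, who consents or how the remaining criteria are applied.

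**An article condenses the full protocol.** Who invites and when allocation is disclosed may be set out elsewhere; the flowchart is not shown, and the Study design section refers to a procedure reported elsewhere. Missing detail alone would be no finding. What remains is a choice made in the text: a visit-based route added beside a more neutral one already in the plan.

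**The analysis will adjust.** Multilevel modelling with confounders and propensity scores should remove part of any imbalance, so unadjusted figures run high. That stands, but such adjustment reaches only what is measured. The confounder list also includes satisfaction and compliance, which Outcome parameters treats as process measures; treatment can affect them, so they cannot stand in for prognosis at entry.

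**Conclusion.** The concern holds as a risk of recruitment bias, not as a demonstrated bias. OPs are the randomised units, they cannot be blinded, a patient's arm follows from the OP, and one of two entry routes works through OP visits during inclusion. The conclusion rests on one assumption that the article implies but does not state: that OPs are allocated before or during patient inclusion.

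The size is unknown. Assumed biases of 0.04 to 0.30 SD correspond to a false-positive rate of about 5% to 21% in an unadjusted, unclustered test with 30 per arm. At 0.30 SD it is about 10% under the protocol's own intraclass correlation. The top of the range needs every patient to be affected, a large baseline shift and no useful adjustment, so it should not be read as a forecast. The change is worth making because selection at entry cannot be fully repaired in the analysis and the means to avoid it are already in the plan.

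**What to change.** 1. Recruit visiting patients by the file-based route. At regular intervals the research team draws visits from the files of all 40 OPs and sends the same letter in both arms.
2. Have the blinded research assistant complete screening, the MINI and all exclusion checks. Obtain consent and any care-giver agreement in the same way in both arms. Finish all of this before the patient and the assessor learn the OP's arm.
3. State when OPs are randomised relative to the first patient invitation.
4. Report numbers invited, eligible and consenting per arm, so that readers can judge whether entry differed.

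The cost is repeated file queries across two companies and slightly slower entry for visiting patients. File selection and a blinded assistant are already planned, although the assistant's task would widen from outcome measurement to entry.

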### Exclusion criteria

Patients will be excluded from the study if they are suicidal, psychotic or suffering from dementia, have insufficient knowledge of the Dutch language to fill in the questionnaires, or are addicted to drugs or alcohol. Patients who are already receiving psychiatric treatment can be included if mutual agreement is achieved with their current care-giver. Patients will also be excluded if they are involved in legislative procedures for unemployment compensation. (See Figure 1 for a flowchart of the participants.)

**Figure 1 F1:**
[figure not shown]
Flowchart of patients.

### Intervention

#### Training

All OPs will receive training in the diagnosis and treatment of common mental disorder in three sessions. They will be trained in the use of tools for screening and diagnostics, and cognitive-behavioural and reattribution techniques. The psychiatrists will be trained to make a diagnosis, and a treatment plan, and to formulate suggestions aimed at RTW specifically tailored to the patient's mental disorder. The psychiatrists will see the patient once and make a written report to the OP by consultation letter. A psychiatrist and an OP from the research group will provide the training.

#### Treatment in the intervention group

The care provided in the intervention group will follow a collaborative care approach: patient-tailored care executed within a team of the OP, the patient, the consulting psychiatrist, and in some cases the General Practitioner (GP). According to a previously developed method[20], a treatment plan will be formulated by the consultant psychiatrist, together with the patient. This will be specifically tailored to the diagnosed common mental disorder, with a focus on RTW. The OP will be informed about the treatment recommended by the consultant psychiatrist. Subsequently, the OP will co-ordinate the care and evaluate the treatment steps. During the consultation, the psychiatrist will make an inventory of treatment that has been offered to the patient before, and will decide, together with the patient, whether more intensive treatment is needed. This depends on the severity of symptoms, the perceived well-being of the patient, and on the level of general functioning according to the GAF score on Axis V of the DSM-IV[38] a method that has been described elsewhere[39].

#### Treatment in the control group

Half of the OPs will be randomized to the control group, and their patients will receive CAU. The actual content of the CAU (e.g. medication, number of contacts with OP, GPs and specialists) will be assessed according to the Scale for Medical Utilisation of Health Services[40].

